#### Self-help plus

Self-Help Plus (SH +) is a transdiagnostic WHO intervention package based on Acceptance and Commitment Therapy that provides tools for guided self-help, empowering participants to manage stress and cope with adversity independently [39, 48]. SH + is delivered by trained, non-specialist facilitators to groups of up to 30 people via a 5-session guided self-help course. The intervention is designed to be adaptable to different cultures and languages. For this study, all SH + materials were professionally translated into Kiswahili following WHO guidelines. The Kiswahili version will be made openly available on the WHO website. The intervention teaches stress management skills through pre-recorded audio files, complemented by guided discussions among participants, using an illustrated guidebook and short audio files to practice skills outside of sessions. Two facilitators support each session by providing additional explanations, demonstrating skills alongside the audio and guiding discussions based on a course manual. The facilitators will receive specialized training from experienced mental health specialists from vivo international Uganda. These specialists will also provide ongoing supervision and support to the facilitators throughout the intervention period. This includes reviewing session plans, observing sessions in-person, providing feedback and guidance to facilitators and addressing any challenges that arise during implementation. This ensures fidelity to the SH + model and supports facilitators in delivering the intervention effectively.

### Criteria for discontinuing or modifying allocated interventions {11b}

Participants are free to withdraw from the study interventions at any time at their own request, without needing to provide a reason. In addition, the research team may discontinue or modify a participant’s allocated intervention if there are concerns about their safety or well-being. Specifically, if a participant experiences a significant clinical deterioration, including the development of severe psychiatric symptoms (e.g. psychosis, suicidality), they will be referred to specialist care within the camp. These participants may still receive the allocated intervention if deemed appropriate by the clinical team. Any deviations from the allocated intervention will be documented.

### Strategies to improve adherence to interventions {11c}

To ensure intervention fidelity and participant adherence, comprehensive training will be provided to all SH + facilitators and model farmers. For the Home Gardening Intervention (HGI), training will be based on a curriculum informed by best practices in sustainable farming and will include hands-on practice. For both interventions, the respective facilitators will undergo an intensive “Training of Trainers” (ToT) program, including theoretical instruction and practical exercises, with a focus on culturally relevant delivery while maintaining fidelity to core components. Ongoing support will be provided to both HGI model farmers and SH + facilitators. For HGI, this includes regular monitoring to support the model farmers through regular in-person visits to participants’ home gardens. For SH +, this includes ongoing supervision from experienced mental health specialists from vivo international Uganda, involving session plan reviews, in-person observation of sessions, feedback and guidance to address challenges. The use of local facilitators who have an understanding of the context and culture will further help to build trust and rapport with participants, thus promoting adherence.

Adherence to the intervention protocols will be monitored through several methods. For HGI, model farmers will complete checklists for each training session to evaluate adherence to the core components of the intervention. Assistant monitors will observe at least 20% of all sessions and complete the same checklists. For SH +, after each session, facilitators will complete a checklist on adherence to the session’s core elements and a post-session review form to document any challenges and feedback that will be reviewed during the regular supervision. SH + supervisors will observe at least 20% of all sessions and complete checklists on facilitators’ adherence to the core components of the session.

### Relevant concomitant care permitted or prohibited during the trial {11d}

Participants will be allowed to receive any usual care available in the Nakivale refugee settlement. There are no prohibitions on concomitant care.

### Provisions for post-trial care {30}

Following the completion of the 12-month follow-up assessments, participants in the EUC arm will be offered the opportunity to receive the HGI training and materials, ensuring that all participants have access to the potential benefits of the agricultural intervention. Additionally, all participants will be provided with information about existing mental health services and support organizations within the Nakivale settlement and surrounding areas. These services may include individual counselling, support groups and referral pathways to specialized care, if needed. There are no provisions for financial compensation for trial participation beyond the refreshments and small transport reimbursements provided during the study. This is in line with common practice in research conducted in humanitarian settings, where resources are often limited. Furthermore, the interventions being evaluated are considered low-risk and potentially beneficial [24, 49], and all participants will receive at least Enhanced Usual Care. Any potential harms will be mitigated as outlined in the “Adverse event reporting and harms {22}” section.

### Outcomes {12}

Trained local enumerators will collect data at three time points: baseline, 3-months post-intervention and 12-months post-intervention. These enumerators will undergo a comprehensive training program of at least 14 full days, covering the administration of all assessment tools, proper interviewing techniques, ethical research conduct and the informed consent process. Data will be captured electronically using the KoboCollect application on tablets. Participants will have the option to complete the assessments in Kiswahili, Kinyabwisha or English, according to their preference.

#### Primary outcome

The primary outcome of this study is food insecurity, which will be measured using the Food Insecurity Experience Scale (FIES) [50] at 12 months post-intervention. The FIES consists of eight questions addressing self-reported food-related behaviors and experiences associated with increasing difficulties in accessing food due to resource constraints. The FIES is unique as it is the most widely used method for evaluating food security at the household or individual level that allows for global comparability [50, 51]. The analysis metric will be the change in the FIES score from baseline to the 12-month follow-up, and the method of aggregation will be the median FIES raw score for each group.

#### Secondary outcomes

Secondary outcomes are focused on mental health and nutritional status, and include:

Mothers’ psychological distress: Measured using the Kessler Psychological Distress Scale (K6) [44] at baseline, 3-month and 12-month follow-ups. The K6 is a six-item questionnaire that assesses symptoms of anxiety and depression. This outcome is important as psychological distress can be both a consequence of food insecurity and a barrier to engaging in adaptive behaviors, such as those promoted by the HGI. The analysis metric will be the change in the K6 score from baseline to each follow-up time point. The method of aggregation will be the mean K6 score for each group. The 3-month assessment will also serve as a manipulation check to verify the effectiveness of the SH + intervention.

Household dietary diversity: Measured using the Household Dietary Diversity Score (HDDS) [52] at baseline, 3-month and 12-month follow-ups. The HDDS is a 12-item questionnaire that assesses the number of different food groups consumed by the household in the previous 24 h. Dietary diversity is a key indicator of diet quality and micronutrient adequacy, which is particularly important for vulnerable populations like refugees [53]. The analysis metric will be the change in the HDDS score from baseline to each follow-up time point. The method of aggregation will be the median HDDS score for each group.

Child malnutrition: Measured as height-for-age z-scores (HAZ) at baseline and 12-month follow-up. Chronic malnutrition, indicated by low HAZ, can have long-term consequences for children’s physical and cognitive development [54]. Height will be measured using a portable stadiometer (model: ALPHA SDM210), and weight will be measured using a digital scale with 50-g accuracy (model: Homebuds HB905). These measurements will be used to calculate HAZ scores based on the WHO Child Growth Standards, which provide age- and sex-specific reference values [55, 56]. The analysis metric will be the change in the HAZ score from baseline to the 12-month follow-up time point. The method of aggregation will be the mean HAZ score for each group.

Figure 1 presents the schematic timeline of enrollment, interventions and assessments, while Table 1 provides a detailed summary of primary and secondary outcome measures.

**Fig. 1 Fig1:**
[figure not shown]
SPIRIT schedule of enrollment, interventions and assessments for the THRIVE trial

**Table 1 Tab1:** Primary and secondary outcomes of the trial

	**Instrument**	**Measure**	**Description**	**End point**	
				**3 mo.**	**12 mo.**
**Primary outcome**					
Food Insecurity	Food Insecurity Experience Scale (FIES) [50, 51]	Median of the FIES raw scores	The FIES was developed by the FAO in collaboration with Gallup and is one of the most widely used measures for tracking global food security in the context of the SDGs [50]	X	X
**Secondary outcomes**					
Maternal Psychological Distress	Kessler Psychological Distress Scale (K6) [44]	Mean score	The K-6 has been used extensively across cultural settings [44], including among South Sudanese female refugees in Uganda [49]	X	X
Household Dietary Diversity	Household Dietary Diversity Score (HDDS) [52]	Median score	The HDDS has been implemented globally in varying survey settings, including in Ethiopia and Uganda [57, 58]	X	X
Child Malnutrition	Height-for-age z-scores (HAZ) [55]	Mean z-score	HAZ is a standardized indicator of chronic malnutrition and long-term growth deficits, validated against WHO Growth Standards [55, 59]. It reliably reflects the cumulative effects of nutritional and health conditions in early childhood [55, 56, 59]		X

Figure 1 illustrates the schematic schedule for Stratum 1. Strata 2 and 3 will follow the same schedule structure, staggered with a two-week delay.

#### Exploratory outcomes

In addition to the primary and secondary outcomes detailed above, we will take advantage of the trial design to collect data on a range of other measures to explore the broader impacts of the interventions on mothers and children. These outcomes span multiple domains including economic preferences, cognitive development, social capital, parenting practices, mental health and general well-being. The results from these ancillary outcome measures will be reported in separate publications focusing on the relevant specific research areas. A full table of exploratory outcomes, including instrument details and descriptions, is available as a supplementary document (Supplementary Table S1).

### Participant timeline {13}

The participant flow diagram is presented in Fig. 2. Following screening, informed consent and enrollment, baseline data collection will be conducted sequentially for each stratum: first for Stratum 1, then Stratum 2 and finally Stratum 3. Villages will be randomly assigned to one of the three study arms after the completion of baseline data collection for each respective stratum. Due to this staggered design, allocation and intervention start dates will vary across the three strata. Enhanced Usual Care (EUC) will be delivered as a single session to all participants before the start of the other interventions. The Home Gardening Intervention (HGI) involves three village-level training sessions and regular monitoring visits, the timing of which will be staggered across strata. The Self-Help Plus (SH +) intervention consists of five group sessions, also staggered across strata. Follow-up assessments will be conducted at 3 and 12 months after the intervention for each participant.

**Fig. 2 Fig2:**
[figure not shown]
SPIRIT flow diagram of the phases of the THRIVE trial

### Sample size {14}

The sample size calculation was conducted using *PowerUp* [60]*!* and was based on the primary outcome of food insecurity. A total sample size of 900 mother–child dyads (300 per arm) is required to detect a between-arm difference in the primary outcome of 0.291 standard deviations with 95% power and an alpha of 0.05. This calculation assumes an intra-cluster correlation coefficient (ICC) of 0.01, based on previous studies in similar settings [61, 62], and accounts for 50% of the variance being explained by individual-level covariates and 20% by cluster-level characteristics. The calculation also assumes a conservative 20% attrition rate at the 12-month follow-up.

### Recruitment {15}

In partnership with local agricultural experts, we will identify villages suitable for the intervention based on feasibility, focusing on those with high concentrations of new arrivals from 2021 to 2025. These individuals often experience significant psychological distress due to limited social support networks and inadequate access to basic resources. Prioritizing these villages aligns with standard livelihood intervention practices in the camp. By focusing on this group, the study aims to provide insights into how targeted support can mitigate these early vulnerabilities and improve adaptation outcomes. Key inclusion criteria for villages are sufficient access to water for home gardening and available agricultural land, while high urbanization levels and current participation in similar programs will be exclusion criteria.

We will include all villages identified in advance with the help of local experts as having concentrations of new arrivals between Q1 of 2021 and Q1 of 2024. During fieldwork, we will then ascertain with the help of local networks in the camp which of the remaining villages have concentrations of new arrivals since Q2 of 2024, and include them sequentially until we have a total of 30 villages. To reach the target number of participants in each village, contiguous villages with smaller concentrations of new arrivals will be grouped into larger units for the purposes of randomization.

Within each selected village, we will compile a list of prospective participants who meet our broad inclusion criteria, identified in conjunction with village leaders, following standard local practices used by established organizations providing livelihood programs in the camp. This list will then be randomly ordered, and individuals will be screened in this order until we reach 30 participants from each village. The random shuffling and selection process will be conducted by an experienced researcher at Bielefeld University who is not otherwise involved in the study. The date of first recruitment was December 13th, 2024.

## Assignment of interventions: allocation

### Sequence generation {16a}

Allocation will be made at the cluster level, stratified according to the settlement patterns of recent arrivals. Stratification will account for three categories based on arrival periods: (1) 2021–2022, (2) 2023 to Q1 2024 and (3) Q2 2024 until recruitment begins. Allocation will follow the Sequentially Numbered Opaque Sealed Envelopes (SNOSE) method [63].

### Concealment mechanism {16b}

The allocation sequence will be concealed using SNOSE, ensuring allocation is unknown until the moment of selection. The envelopes will contain a folded paper indicating the assigned treatment arm (EUC, HGI or SH + HGI). The principal researcher in Uganda will prepare these envelopes, which will be sequentially numbered and opaque to prevent prediction or manipulation.

### Implementation {16c}

The unmasked principal researcher in Uganda will oversee the preparation of the sealed envelopes. The SNOSE procedure will take place, one stratum at a time, in a meeting attended by village leaders or their representatives. The randomization procedure will be explained, after which each village representative will draw a sealed envelope containing the treatment assignment. The research team will not influence or intervene in the selection process. Participants within each village will then be assigned to the intervention arm allocated to their village.

## Assignment of interventions: blinding

### Who will be blinded {17a}

Due to the nature of the interventions, blinding of participants is not feasible. Data collectors will be blinded to the village allocations.

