### Who will take informed consent? {26a}

Informed consent will be obtained from all participating mothers by trained local enumerators, supervised by the on-site principal researcher. The enumerators will undergo thorough training on the screening, consent procedures and ethical considerations involved in the study. The enumerators will present an informed consent form to all eligible participants, explaining the purpose of the study, the procedures involved, the potential risks and benefits of participation, data confidentiality and the participants’ right to withdraw from the study at any time without penalty. Mothers will be asked to provide parental consent for their child’s inclusion in the study, and the children will be asked to assent. Literate participants will provide their consent by signing the informed consent form. For participants who are illiterate, a thumbprint will be used as a valid form of consent, with a witness present during the consent process.

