#### Home gardening intervention

The HGI is designed to promote climate-smart farming techniques, empowering participants to achieve greater self-sufficiency [24]. The intervention provides training on growing nutrient-dense crops on small plots near participants’ homes, emphasizing year-round cultivation, sustainable farming practices and knowledge transfer [47]. The HGI utilizes a four-pronged strategy: (1) supplying tools, seeds, and other essential materials; (2) offering education on home-based sustainable agricultural practices; (3) providing lessons on nutrition and cooking; and (4) teaching sustainable harvesting and market strategies.

The program starts with a 3-day training of trainers (ToT) for 20 model farmers and the monitoring team, led by senior trainers specializing in sustainable agriculture. Village-level training of the participants includes three in-person sessions with senior trainers at model farmers’ plots, each lasting approximately 6 h, with at least 2 h devoted to hands-on practice. The timing of these sessions will be staggered across the three strata. Thereafter, trained model farmers located in each village will provide continual support to participants throughout the intervention period. Each participant will receive regular in-person visits at their home garden from a model farmer or assistant monitor.

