## Data collection and management

### Plans for assessment and collection of outcomes {18a}

Primary and secondary outcome data along with sociodemographic characteristics and potential confounders will be collected electronically using tablets equipped with KoboCollect software. Data collection will occur at baseline, 3-month and 12-month post-intervention. Baseline and 12-month follow-up assessments will be conducted in person at a central location, while 3-month follow-up assessments will be conducted at participants'homes to minimize travel burden. Local enumerators, trained by the research team, will administer the surveys and assessments. The training will cover the administration of assessment tools, general interviewing techniques and ethical conduct of research. All measures will be available in English, Kiswahili and Kinyabwisha, depending on the preferred language of the participant. Table 1 provides a summary of the primary and secondary outcomes, including their validation status. The data collection forms are available on request. To ensure data quality, the core research team in Uppsala will conduct daily checks on the number of records uploaded and the completeness of these records.

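### The stated blinding of data collectors probably fails for gardening versus EUC at the 3-month home interviews, which puts the 12-month FIES at risk if the same enumerators return

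*Protocol article*

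**What the plan says.** All references are to the protocol article.

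- **Blinding {17a}.** For participants: "Due to the nature of the interventions, blinding of participants is not feasible". For assessors: "Data collectors will be blinded to the village allocations". Section {17b} adds that unblinding will not be needed.
- **Place of assessment {18a}.** "Baseline and 12-month follow-up assessments will be conducted in person at a central location", but "3-month follow-up assessments will be conducted at participants'homes to minimize travel burden". Table 1 shows that FIES, K6 and HDDS are collected at month 3; HAZ is not.
- **Home gardening intervention.** HGI offers "training on growing nutrient-dense crops on small plots near participants" (the phrase continues to their homes). Tools, seeds and other materials are supplied, and a model farmer or assistant monitor regularly visits the home garden.
- **Comparator {6b}.** EUC mothers are given HGI only once the 12-month data are in.
- **Enumerators {12}.** Trained local enumerators are described as one group covering baseline, month 3 and month 12.
- **Missing data {20c}.** LOCF is allowed for missing follow-up data among completers.

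**The concern.** The blinding claim and the place of the 3-month interviews do not sit well together. An enumerator who interviews at home in an HGI or SH + HGI village is close to the plots and supplied materials; in an EUC village there is no HGI to see. Because whole villages share an arm, with 30 dyads in each, an enumerator who makes several visits sees a pattern and not one ambiguous plot. What is learned applies to every mother in that village.

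The primary outcome is a self-report taken by interview from mothers who know their arm. Assessor blinding is thus one of the few safeguards available for the 12-month FIES, and readers of the trial will rely on the statement in {17a}. If it does not hold, knowledge of arm could influence how questions are put or answers recorded, mainly in the EUC versus HGI comparison.

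**Working it through.** **1. The sections side by side**

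| Question | Month 3 | Month 12 |
|---|---|---|
| Where is the interview? | Participant's home {18a} | Central location {18a} |
| Is an HGI garden nearby in HGI and SH + HGI villages? | Yes, plots are near homes | Not at the interview site |
| Is HGI present in EUC villages? | No {6b} | No {6b} |
| Who interviews? | Trained enumerators {12} | Trained enumerators {12}; whether the same person meets the same village is not stated |
| Outcomes exposed | FIES, HDDS, K6, directly | FIES, HDDS, K6, only through what was learned at month 3 |

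Two things follow. At month 3 the blind for gardening versus EUC cannot be relied on. At month 12 exposure depends on one further condition: that an enumerator meets mothers from a village visited at month 3.

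A second route needs no returning enumerator. If LOCF under {20c} fills a missing 12-month FIES, a home-interview value becomes the primary endpoint value for that mother.

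**2. Reproducing the design figure**

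Inputs from Sample size {14}: 300 dyads per arm, ICC 0.01, 50% of individual-level and 20% of cluster-level variance explained, 20% attrition, alpha 0.05, power 95%. From Trial design {8}: 30 villages in three arms, so J = 20 villages per pairwise contrast and P = 0.5. Analysed per village: n = 30 × 0.8 = 24. Assumed: df = 20 − 2 − 1 = 17 (one cluster-level covariate).

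- SE² = ICC(1 − R²_cluster)/[P(1 − P)J] + (1 − ICC)(1 − R²_ind)/[P(1 − P)Jn]
- = 0.01 × 0.80/5 + 0.99 × 0.50/120 = 0.001600 + 0.004125 = 0.005725
- SE = 0.0757 SD
- Minimum detectable difference = (t₀.₉₇₅,₁₇ + t₀.₉₅,₁₇) × SE = 0.2913 SD, against the stated 0.291

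The plan's figure reproduces, so this SE is a fair scale for the illustration.

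**3. Illustration under an assumed bias**

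The size of any assessor bias is an assumption; nothing in the documents fixes it. Take one pairwise contrast with no true effect, a uniform shift b in one direction, and a two-sided 5% test with noncentrality b/SE on 17 df.

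| Assumed b (SD) | Share of 0.291 | b/SE | Rejection rate under the null |
|---|---|---|---|
| 0 | 0% | 0 | 5.0% |
| 0.05 | 17% | 0.66 | 9.6% |
| 0.10 | 34% | 1.32 | 23.9% |

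The shift is an average over the contrast. If an aware enumerator moved FIES by 0.10 SD but only half of the relevant interviews were affected, b = 0.5 × 0.10 = 0.05 SD and the 9.6% row applies. The figures also treat H1 as a stand-alone test. Section {20a} makes pairwise comparisons only after a significant intervention-by-time interaction, so they are upper bounds for the assumed b.

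**The case against.** Several points on the other side are sound.

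- **A plot does not prove the arm.** Under Eligibility criteria {10}, every mother has access to farmable land, and villages were chosen for water and agricultural land. EUC villages can have cultivated plots. This stands: recognition of the arm at month 3 is a strong inference, not a stated fact.
- **The primary endpoint is collected elsewhere.** A reader might infer that blinding is already lost for month 12. The documents do not support that. The interview is at a central site, and {12} does not say who is assigned to which village. An article may leave such rotas to a field manual. The risk remains because {12} suggests a common pool of enumerators.
- **Gardens do not reveal full allocation.** They separate EUC from the two gardening arms but not HGI from SH + HGI, so H2 is not unblinded by this route.
- **The supervisor.** A reader might link {26a}, where enumerators taking consent are "supervised by the on-site principal researcher", with {16c}: "The unmasked principal researcher in Uganda will oversee the preparation of the sealed envelopes". This shows no loss of blinding. Under Participant timeline {13}, consent and baseline precede randomization in each stratum, so there is then no allocation to disclose, and nothing says that allocations reach enumerators later.
- **Respondents are unblinded anyway.** Their own reporting bias remains whatever the enumerator knows. True, but that is no reason to add a second source of bias.

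None of this reconciles the unqualified sentence in {17a} with interviews held close to the gardens.

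**Conclusion.** The point holds in a limited form. The statement in {17a} cannot be relied on at month 3 for gardening versus EUC. The 3-month FIES, HDDS and K6 are directly exposed for that contrast. For the 12-month FIES there is a risk to H1, conditional on enumerators meeting mothers from villages they visited at month 3, or on LOCF carrying home-interview values forward. H2 is not affected by the gardens alone.

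The conclusion rests on the places and timing set out in the article, not on a calculation. The rise in type I error to about 10% to 24% describes only what an assumed uniform bias of 0.05 to 0.10 SD would do. It is not an estimate of what will happen. The matter should be corrected; it does not threaten the design.

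**What to change.** 1. **Rota.** Assign existing enumerators so that nobody interviews at month 12 a mother from a village they visited at month 3. It can be drawn up from the village list without the allocations. Month-3 visits must be planned with this in mind, so that no enumerator covers every village.
2. **Check on the blind.** Add one item to the 12-month form recording the enumerator's guess of arm. Asking for the reason as well helps, since a guess may merely reflect the FIES answers.
3. **Wording of {17a}.** State that 3-month home assessments are not reliably blinded for gardening versus EUC, and say how 12-month assessors are assigned.
4. **Missing 12-month FIES.** Because {20c} allows LOCF, state that 3-month home-interview FIES values will not be substituted for missing 12-month values.

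The central location for month 12 and the blinding of collectors to allocations are already in the plan and need only be kept.

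**Cost.** A rota among existing staff, one form item and two sentences of text. The downside is less flexible scheduling and some loss of rapport when mothers meet a new interviewer. Sample size, interventions and endpoints do not change. According to Trial status, baseline collection was still under way at submission, so both follow-ups then lay ahead.
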